### Associated mechanisms

To delineate the functional and neurophysiological changes that are associated with the effects of BATRAC and CIMT, three additional tests will be administered before and after intervention, and after the retention period.

### Peripheral stiffness

Endpoint mechanical behavior of the paretic wrist, resulting from a mix of visco-elastic (intrinsic) and proprioceptive reflex (reflexive) properties, will be assessed under both passive and active conditions using a haptic robot ('Wristalyzer', Moog FCS Inc., Nieuw-Vennep, The Netherlands). This powerful, force-controlled manipulator applies force- and position perturbations to the paretic wrist, while the interaction with the patient, in terms of forces and joint angles, is measured. A haptic controller, which overrules the dynamics of the manipulator with imposed virtual dynamics, is used to apply perturbations. The result is that, to the patient, the manipulator behaves like a mass-spring-damper system. After assessment of the range of motion (ROM) and maximal force, both towards flexion and extension, a number of perturbation tests under both passive and active conditions will be applied. Using system identification in the frequency domain [39,95,96], the intrinsic vs. reflexive stiffness is calculated from the time series of net moment and wrist position. Surface EMG (16-channel Biotel 99 EMG amplifier, Glonner Electronic GmbH, Munich, Germany) is measured for additional validation. From the time records of position and force, frequency response functions (FRFs) will be estimated. FRFs are transfer functions that express the structural response to an applied force in the frequency domain. Given a model structure and an appropriate estimate of the intrinsic component, an estimate of the reflex gains for length and velocity can be obtained from the FRFs [39,95,96]. For both intrinsic and reflexive properties, a repeated measures AN(C)OVA will be performed to detect differences over time and between groups (intervention/stratification).

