**Methods/Design:**

Sixty patients with a first ever stroke will be recruited. Patients will be stratified in terms of their remaining motor ability at the distal part of the arm (i.e., wrist and finger movements) and randomized over three intervention groups receiving modified CIMT, modified BATRAC, or an equally intensive (i.e., dose-matched) conventional treatment program for 6 weeks. Primary outcome variable is the score on the Action Research Arm test (ARAT), which will be assessed before, directly after, and 6 weeks after the intervention. During those test sessions all patients will also undergo measurements aimed at investigating the associated recovery mechanisms using haptic robots and magneto-encephalography (MEG).

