### Power analysis

The number of patients is based on a statistical power of 80% (preventing Type II error) with an alpha of 5% (preventing Type I error) for detecting a meaningful difference of 6 points on the ARAT as the primary measurement of outcome and expecting 15% drop-out. The statistical power for detecting 10% or 6 points difference between groups is based on the following power calculation:

(Z_1-α/2 _+ Z_1-β_)^2 ^= 10.43 (assuming an alpha of 0.017, corrected for multiple testing with 3 groups and a Beta of 0.80)

σ2 (expected variance of sample on ARAT) = 26

Δ2 (assumed difference in favour ARAT) = 36

r (expected ratio between intervention groups) = 1

Expected numbers needed per intervention group (N_per group_) = 15 (excluding expected drop out of less than 25%).

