### Interlimb interactions

Ridderikhoff et al. [71] devised an experimental methodology to dissociate between the contributions of three sources of interlimb interaction: integration of feed-forward control signals to both hands; error correction of the phasing between the hands, based on afferent signals; and (unintended) phase entrainment by contralateral afferent signals, probably resulting from spinal reflexes. It is based on systematic comparisons between four coordination tasks involving bimanual performance (in- and antiphase coordination) and unimanual performances with and without comparable motor-driven movements of the contralateral hand. The four tasks are the following: (a) unimanual rhythmic coordination with an auditory pacing signal (UN); (b) idem, while the contralateral hand is moved passively with a phase shift of 30° with respect to the required movements of the active hand (UNm); (c) kinesthetic tracking (KT): unimanual active movements are to be coordinated (in- or antiphase) with the passive rhythmic movements of the contralateral hand; and (d) active auditorily-paced bimanual coordination (in- or antiphase; AB). The tasks are performed in an experimental set-up in which passive movements can be imposed using a servo-motor (Parvex RS440GR1031, SSD Parvex SAS, Dijon Cedex, France) and a precision gearbox (alpha TP010S-MF1-7-0C0, backlash ± 0.02°, Wittenstein, Inc., Bartlett, IL, USA), and the active movements are measured using potentiometers (FCP40A, tolerance ± 0.1%, Sakae Tsushin Kogyo Co., Ltd., Nakahara-ku, Kawasaki-city, Japan). Depending on the task conditions, the motor-driven, passive movements are based on either the movements of the to-be-moved hand as recorded during condition (d), which is therefore the first task to be performed, or a predefined sinusoidal pattern (with added random noise). Given the inherent functional asymmetry in the subject population of interest, tasks (a)-(c) are performed with both the paretic and the non-paretic hand as active hand (order counterbalanced over subjects). The Analysis focuses on the relative phase between both hands in bimanual tasks (i.e., AB and KT) and between the active hand and the metronome in the unimanual tasks (i.e., UN and UNm). Mean relative phase and circular standard deviation will be used to dissociate between the contributions of three sources of interlimb interaction after each test separately (i.e., t0, t1, and t2; *t*-tests and repeated measures ANOVA), and to detect changes in these over the three tests (repeated measures AN(C)OVA). Additionally, correlations between the durations of simultaneously performed cycles (as an index of degree of coupling), and correlations between the error in the discrete relative phase and the duration of the following cycle of the non-affected hand (as an index of the effectiveness of error corrections), will be calculated for the tasks that involve two moving hands (i.e., AB, KT, UNm). These correlations will be transformed into normally distributed variables using the Fisher transform. A repeated measures AN(C)OVA will be used to examine the changes over time.

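### Repeated measures AN(C)OVA over three sessions is an inefficient choice for the stiffness and interlimb outcomes when drop-out is expected; a mixed model would keep the t0-t1 data of patients who miss t2

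*Protocol article*

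**What the plan says.** The Associated mechanisms section of the protocol article schedules the mechanism tests before the intervention, after it and after the retention period (t0, t1, t2).

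- **Peripheral stiffness:** "For both intrinsic and reflexive properties, a repeated measures AN(C)OVA will be performed to detect differences over time and between groups (intervention/stratification").
- **Interlimb interactions:** repeated measures AN(C)OVA is named for changes in mean relative phase and circular standard deviation across the three sessions. For the Fisher-transformed correlations the text says: "A repeated measures AN(C)OVA will be used to examine the changes over time". The section also plans t-tests and repeated measures ANOVA within each session on its own.
- **Power analysis:** two drop-out figures appear, both within the ARAT calculation. One is 15%; the other qualifies the required number per group: "excluding expected drop out of less than 25" per cent.
- **Abstract, Methods/Design:** "Sixty patients with a first ever stroke will be recruited".

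The article does not say how a patient with a missed session enters the analyses over time.

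**The concern.** A classical repeated measures AN(C)OVA with three levels of time needs a value at each level for every patient. A patient measured at t0 and t1 but not at the retention test then contributes nothing, not even to the t0-t1 change. That change speaks most directly to what the interventions induce, although the article names no main contrast for these outcomes. The method also assumes sphericity unless a correction is applied. Complete-case analysis generally needs a stronger missing-data assumption than a likelihood-based mixed model.

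Delineating functional and neurophysiological change is one of the program's two stated aims. The stiffness analysis compares groups by intervention and by stratum, which spreads 60 patients over 3 x 2 = 6 cells, or 10 per cell on average. With 45 to 51 complete patients the average is 7.5 to 8.5. Observed t0-t1 pairs are too few to give up without reason.

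**Working it through.** **1. The plan's own figure.** Inputs from Power analysis: squared sum of normal quantiles 10.43; "σ2 (expected variance of sample on ARAT) = 26"; "Δ2 (assumed difference in favour ARAT) = 36"; equal group sizes.

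n per group = 2 x 26 x 10.43 / 36 = 15.07, against the stated 15.

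- With 25% drop-out: 15 / 0.75 = 20 per group, or 60 in all.
- With 15% drop-out: 15 / 0.85 = 17.6, rounded up to 18 per group, or 54 in all.

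The 60 recruited therefore match an allowance of 25%. This calculation concerns the ARAT only; the article gives no power figure for the mechanism outcomes.

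**2. Complete patients.** If the ARAT drop-out figures also hold for the robot and interlimb sessions (an assumption):

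- 60 x 0.85 = 51 complete, 9 incomplete;
- 60 x 0.75 = 45 complete, 15 incomplete. This is the limiting case, since the article says less than 25%.

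**3. Cost to the t0-t1 contrast.** Assumptions, none given in the article: equal variances and a common correlation ρ between sessions (compound symmetry), ρ from 0.5 to 0.9, known covariance, monotone drop-out unrelated to outcome, and the same pattern in each arm. Let d be the drop-out proportion and s the share of drop-outs who leave after t1. Per arm of size n, in units of the outcome variance:

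- complete cases: V_cc = 2(1 - ρ) / [n(1 - d)];
- mixed model: V_mm = (1 - ρ²) / [n(1 - d(1 - s))] + (1 - ρ)² / n.

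The ratio is

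V_cc / V_mm = 2 / {(1 - d) x [(1 + ρ) / (1 - d(1 - s)) + (1 - ρ)]}.

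With s = 1 it reduces to 1 / (1 - d). With s = 0 it reduces to 2 / [2 - d(1 - ρ)].

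Example, d = 0.25, s = 0.5, ρ = 0.5: 2 / {0.75 x [1.5 / 0.875 + 0.5]} = 2 / 1.661 = 1.204.

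| When drop-outs leave | d = 15% | d = 25% |
|---|---|---|
| All before t1 (s = 0) | 1.01-1.04 | 1.01-1.07 |
| Half before, half after (s = 0.5) | 1.09-1.11 | 1.17-1.20 |
| All after t1 (s = 1) | 1.18 | 1.33 |

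Ranges run over ρ = 0.9 to 0.5. On the standard-error scale (square root), the middle row is a loss of about 5% at d = 15% and 8-10% at d = 25%.

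**4. Other contrasts.** The loss is smaller. With half leaving early and half late, t0-t2 gives 1.03-1.05 (15%) and 1.05-1.08 (25%), and t1-t2 gives 1.02-1.03 and 1.04-1.05. Even if all leave after t1, both contrasts stay at 1.04-1.05 (15%) and 1.07-1.09 (25%).

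**The case against.** The strongest reply is that the article nowhere says incomplete patients are deleted or that sphericity goes uncorrected. It is a condensed publication, and rules for missed sessions commonly sit in the full protocol or the analysis plan, which are not shown. That stands as far as it goes: exclusion is inferred from the usual form of the named method, and a reader should not report it as a stated rule. The choice of method, however, is stated, and it is the choice that is questioned here.

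Other readings that go too far:

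- **That every interlimb analysis loses these patients.** The tests within a single session lose only the session that was missed. The point covers the analyses over time.
- **That the plan forecasts 15-25% drop-out for these outcomes.** It gives two separate figures that do not agree, both for the ARAT.
- **That the trial becomes underpowered or its primary result is affected.** The 60 patients already absorb 25% loss in the ARAT calculation, and ARAT improvement is analysed by Kruskal-Wallis and Mann-Whitney tests.
- **That the results would be biased.** Nothing in the article or the calculation shows this; the calculation takes drop-out to be unrelated to outcome and so speaks only to precision.

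It is also fair to say that the gain depends on when patients leave, on which the article is silent. It nearly vanishes if they leave before t1. A mixed model, for its part, leans on a covariance structure estimated from few patients.

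**Conclusion.** The point holds in a limited form and at low severity. For the stiffness and interlimb analyses over t0, t1 and t2, the named method in its standard form sets aside observed data that a mixed model would use.

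If the ARAT drop-out figures carry over, 9 to 15 of 60 patients would be incomplete. Under the stated assumptions the t0-t1 contrast has 9-11% more variance at 15% drop-out and 17-20% more at 25% when departures are split evenly around t1. The extremes are 1-7% if all leave before t1 and 18-33% if all leave after. These figures rest on assumed correlation, timing and unrelated drop-out, and they treat the covariance as known, so they slightly flatter the mixed model in a sample this small.

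The consequence is lower precision in supporting mechanism outcomes for which no power is claimed.

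**What to change.** For the analyses over time in Peripheral stiffness and Interlimb interactions, replace repeated measures AN(C)OVA by a linear mixed model on all available t0, t1 and t2 values:

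- **Fixed effects:** arm, time, stratum and their interactions, including arm-by-time-by-stratum. A stratum main effect alone would not do. The Background section expects modified BATRAC to reduce stiffness effects more than modified CIMT specifically in participants with minimal hand and finger control, and the stiffness analysis itself compares groups by stratum.
- **Covariance:** unstructured over the three sessions. A random patient intercept alone imposes compound symmetry, which is stricter than sphericity.
- **Inference:** Kenward-Roger degrees of freedom, with the t0-t1, t0-t2 and t1-t2 arm contrasts taken from the one model.
- **Interlimb outcomes:** keep the task, coordination-mode and active-hand factors, or fit the model to each derived measure separately.

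The tests within single sessions can stay as they are. If the sponsor prefers to keep AN(C)OVA, the least needed is a sentence saying how patients with a missed session are handled.

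Cost: a short rewording of the analysis text in two sections, slightly more modelling work (more for the interlimb outcomes because of their task factors), and reliance on a covariance model in a small sample. For a single measure per session the model has 3 x 3 x 2 = 18 cell means and 6 covariance parameters. No extra data are needed.

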### Interlimb interactions

Ridderikhoff et al. [71] devised an experimental methodology to dissociate between the contributions of three sources of interlimb interaction: integration of feed-forward control signals to both hands; error correction of the phasing between the hands, based on afferent signals; and (unintended) phase entrainment by contralateral afferent signals, probably resulting from spinal reflexes. It is based on systematic comparisons between four coordination tasks involving bimanual performance (in- and antiphase coordination) and unimanual performances with and without comparable motor-driven movements of the contralateral hand. The four tasks are the following: (a) unimanual rhythmic coordination with an auditory pacing signal (UN); (b) idem, while the contralateral hand is moved passively with a phase shift of 30° with respect to the required movements of the active hand (UNm); (c) kinesthetic tracking (KT): unimanual active movements are to be coordinated (in- or antiphase) with the passive rhythmic movements of the contralateral hand; and (d) active auditorily-paced bimanual coordination (in- or antiphase; AB). The tasks are performed in an experimental set-up in which passive movements can be imposed using a servo-motor (Parvex RS440GR1031, SSD Parvex SAS, Dijon Cedex, France) and a precision gearbox (alpha TP010S-MF1-7-0C0, backlash ± 0.02°, Wittenstein, Inc., Bartlett, IL, USA), and the active movements are measured using potentiometers (FCP40A, tolerance ± 0.1%, Sakae Tsushin Kogyo Co., Ltd., Nakahara-ku, Kawasaki-city, Japan). Depending on the task conditions, the motor-driven, passive movements are based on either the movements of the to-be-moved hand as recorded during condition (d), which is therefore the first task to be performed, or a predefined sinusoidal pattern (with added random noise). Given the inherent functional asymmetry in the subject population of interest, tasks (a)-(c) are performed with both the paretic and the non-paretic hand as active hand (order counterbalanced over subjects). The Analysis focuses on the relative phase between both hands in bimanual tasks (i.e., AB and KT) and between the active hand and the metronome in the unimanual tasks (i.e., UN and UNm). Mean relative phase and circular standard deviation will be used to dissociate between the contributions of three sources of interlimb interaction after each test separately (i.e., t0, t1, and t2; *t*-tests and repeated measures ANOVA), and to detect changes in these over the three tests (repeated measures AN(C)OVA). Additionally, correlations between the durations of simultaneously performed cycles (as an index of degree of coupling), and correlations between the error in the discrete relative phase and the duration of the following cycle of the non-affected hand (as an index of the effectiveness of error corrections), will be calculated for the tasks that involve two moving hands (i.e., AB, KT, UNm). These correlations will be transformed into normally distributed variables using the Fisher transform. A repeated measures AN(C)OVA will be used to examine the changes over time.

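### The supplementary error-correction index is tied to the non-affected hand, which the motor drives in KT and UNm whenever the paretic hand is active, so it cannot show correction in those two cells

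*Protocol article*

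**What the plan says.** All of the relevant text stands in one section of the protocol article, Interlimb interactions (Methods).

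- **Definition.** The index is built from "correlations between the error in the discrete relative phase and the duration of the following cycle of the non-affected hand" and is intended "as an index of the effectiveness of error corrections".
- **Scope.** Together with a coupling index, it "will be calculated for the tasks that involve two moving hands (i.e., AB, KT, UNm"). No exception is made according to which hand is active.
- **Active hand.** Because the patients are functionally asymmetric, "tasks (a)-(c) are performed with both the paretic and the non-paretic hand as active hand". Tasks (b) and (c) are UNm and KT, so both are also run with the paretic hand active.
- **The other hand in UNm.** The patient moves one hand to an auditory pacing signal "while the contralateral hand is moved passively with a phase shift of 30" degrees, set against the movements required of the active hand.
- **The other hand in KT.** Here "unimanual active movements are to be coordinated (in- or antiphase) with the passive rhythmic movements of the contralateral hand".
- **Source of the passive movement.** A servo-motor imposes it, "based on either the movements of the to-be-moved hand as recorded during condition (d") or on "a predefined sinusoidal pattern (with added random noise").
- **Rank of the index.** The section's main measures are the mean and the circular standard deviation of relative phase, analysed at t0, t1 and t2. The correlations are introduced as an addition to these, and the stated model for them examines change over time.

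**The concern.** An index of error correction has to relate a phase error to what the correcting hand does next. A hand moved by a motor along a trajectory fixed beforehand does not correct anything. As defined, the index follows the non-affected hand even in the runs where that hand is the one being driven. In those runs, the correlation describes the imposed signal and not the patient.

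The same definition means that this index never reads the next cycle of the paretic hand. The section has both hands tested as active hand because of the patients' asymmetry, and the index makes no use of the paretic-active half of that information.

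Interlimb interactions belong to the second research question in the Background, and error correction is one of the three sources of interaction that the section sets out to separate. At stake is whether this supplementary measure can contribute anything from the paretic-active runs. An analysis script written from this text would produce values for those cells that look like data but carry no information about correction.

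**Working it through.** The document gives no figure for this index, so there is none to reproduce. The check sets the statements above side by side, for each task and active hand.

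| Cell | State of the non-affected hand | Hand whose next cycle is used | Can the index reflect correction? |
|---|---|---|---|
| AB | active | non-affected | yes, for that hand only |
| KT, non-paretic active | active | non-affected | yes, for that hand |
| UNm, non-paretic active | active | non-affected | refers to the active hand, but the phase error used is not stated |
| KT, paretic active | motor-driven | non-affected | no |
| UNm, paretic active | motor-driven | non-affected | no |

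Counts:

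- Motor-driven cells: 2 tasks × 2 active hands = 4.
- Cells in which the index refers to the driven hand: 2 of 4.
- Cells in which it uses the paretic hand's next cycle: 0 of 5 (the 4 cells plus AB).

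The step that matters is that the motor does not react to the patient. Both sources of the passive movement, replay and preset sinusoid, are fixed before the run starts. In UNm the phase shift is set against the required movement of the active hand and not its actual movement. Nothing described feeds the patient's error back to the motor.

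A small simulation of KT with the paretic hand active shows what the correlation would look like. Its inputs are assumptions and do not come from the document: 1 s mean cycle, 0.04 s noise SD, 30 cycles, 4000 runs, linear phase correction with gain g, and correlations averaged on the Fisher scale. At cycle k:

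- error e(k) = onset of the active hand − onset of the driven hand
- next active (paretic) cycle = 1 − g·e(k) + noise
- next driven (non-affected) cycle = preset, with no dependence on e(k). For the sinusoid with noise it is 1 + independent noise. For the replay it is the difference between successive onsets scattered round the metronome.

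| Passive movement | g | r with next driven cycle (as written) | r with next active cycle |
|---|---|---|---|
| Sinusoid + noise | 0.1 | 0.13 | −0.34 |
| | 0.3 | 0.08 | −0.53 |
| | 0.6 | 0.05 | −0.69 |
| | 0.9 | 0.03 | −0.80 |
| Replay | 0.1 | 0.39 | −0.32 |
| | 0.3 | 0.43 | −0.51 |
| | 0.6 | 0.45 | −0.72 |
| | 0.9 | 0.43 | −0.84 |

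As written, the index hardly follows the true gain. Under the sinusoid it is a small-sample bias that shrinks towards zero. Under replay it sits near 0.4 because of serial correlation in the replayed cycles. On the active hand it follows the gain closely. The replay values also show that the fault need not be visible in the data, since the correlation is not zero even though no correction takes place in the driven hand.

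**The case against.** The best defence is that this is a slip of wording in a condensed article. The sentence may have been meant to say the active hand, and the working definition may stand in the full protocol or in the cited methodology paper, neither of which is at hand. That is possible, and it limits the claim to the text: what will actually be computed is not known. But this is not an omission. The article states a definition, the same section uses active hand as a separate term, and nothing else in the article redefines the index. Nor does it help to suppose that only runs with the non-paretic hand active were meant, because the text does not say so.

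A second defence is that the index is a minor one. This stands. It is an addition within one of three mechanism tests.

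Two stronger readings are tempting, and the document does not support them:

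- A reader might infer that corrections by the paretic hand go unmeasured in the whole trial. They do not. KT is run with the paretic hand active, and its mean relative phase and variability are among the main measures at every assessment. The count of 0 of 5 applies to this correlation alone.
- A reader might infer that comparisons between arms would be misread. This is not shown. For these correlations the section states only an analysis of change over time. The Background does expect modified BATRAC to improve interlimb interactions more than the other arms, but it does not name this index. The simulation points to an uninformative measure in the affected cells and does not demonstrate a spurious training effect.

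**Conclusion.** The definition is wrong as written for KT and UNm with the paretic hand active, which is 2 of the 4 motor-driven cells. There the index cannot reflect error correction, and nowhere does it use the paretic hand's next cycle. It remains valid for the non-affected hand in AB and in KT with that hand active. For UNm with that hand active, the index refers to the right hand, but the phase error needs to be stated.

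The conclusion follows from the text and rests on one premise, that the driven movement is fixed in advance, as both described sources imply. It does not depend on the simulation, which is illustrative and uses assumed inputs. The ARAT analysis, the clinical secondary outcomes and the sample size are not affected. This is a definition that should be corrected before the mechanism data are analysed. It is not a threat to the trial's main result.

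**What to change.** Needed: for KT and UNm, define the index on the following cycle of the active hand instead of the non-affected hand. For UNm, also state which phase error enters the correlation, because the section's main analysis refers UNm phase to the metronome and not to the other hand.

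Worth adding at no cost: in AB, where both hands are active, compute the index for each hand separately.

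Treating the two hands as separate levels in the repeated-measures model, or reading the UNm value as entrainment instead of correction, are matters of preference that nothing in the text requires.

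The cost is one changed definition in the analysis plan and script. The section already has active movements measured by potentiometers, and KT and UNm are already run with each hand active, so no further recordings or assessments are needed.
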